## Abstract

**Background:**

Silver diamine fluoride (SDF) solution is effective in arresting early childhood caries (ECC). Previous studies have suggested that it might exert a preventive effect in managing ECC. However, no well-designed clinical trials have yet been performed to study the effect of SDF on caries prevention. The objective of this randomised clinical trial is to determine whether 38% SDF solution is superior to 5% sodium fluoride (NaF) varnish in preventing new carious lesions in primary anterior teeth.

**Methods/design:**

This is a phase II, single-centre, randomised, double-blind, active-controlled, parallel-group pragmatic trial. The hypothesis tested is that 38% SDF would be more effective than 5% NaF in preventing new caries development in primary anterior teeth. Approximately 730 3-year-old children who are generally healthy and with parental consent will be recruited from Hong Kong kindergartens. This sample size will be sufficient for appropriate statistical analysis of a superiority trial with 90% power, allowing for a 20% drop-out rate. Stratified randomisation will be adopted for allocating the intervention. The intervention will either be 38% SDF or 5% NaF (as a positive control) therapy on primary upper anterior teeth. A single trained examiner will conduct a dental examination every 6 months until 30 months in kindergarten. Another operator will provide fluoride therapy immediately after each dental examination. The examiner, children and children’s parents will be blinded to the treatment allocation. A questionnaire survey will be conducted to study the children’s oral health-related behaviours and socioeconomic backgrounds. Chi-square tests, *t* tests, regression analyses and survival analyses will be adopted for data analysis.

**Discussion:**

The effectiveness of 38% SDF in preventing ECC remains uncertain. If the results are as anticipated, care standards using 5% NaF for ECC prevention will be changed. In addition, the results will be widely available and increase the adoption of SDF in other countries to reduce the global burden of ECC.

**Trial registration:**

ClinicalTrials.gov, NCT04075474. Registered on 30 Aug 2019.

## Background

Early childhood caries (ECC) is the single most common chronic childhood disease, and its development is a global health problem [1]. In the United States, nearly half of children have ECC before entering kindergarten [2]. More than half of 5-year-old Hong Kong children suffer from ECC, and around 90% of the caries are left untreated [3]. In the Philippines, the main reason for absence from school is dental caries [4]. Because the prevalence of dental caries in children aged 2 to 5 years has recently increased globally, the World Dental Federation (FDI) has prioritised this age group [5]. ECC causes pain and infection, and advanced caries will progress into the tooth pulp to eventually form a dental abscess [6]. Cases that remain untreated will lead to tooth loss, which can affect dentition. More importantly, poor dentition significantly affects children’s nutrition and consequently their growth, development and general health [7].

Although the FDI Oral Health Atlas has reported that millions of children are suffering from untreated ECC, along with a great shortage of community dentists, the present dental care delivery system cannot cope with the high ECC prevalence worldwide [8]. The FDI promotes the use of fluoride to prevent ECC in children through health-promotion strategies and programmes [9]. Although sodium fluoride (NaF) varnish is considered a standard of care in preventing ECC, a systematic review by the Cochrane Collaboration revealed that applying 5% NaF varnish (containing 22,600 ppm fluoride) is inadequate because it reduced only 37% of ECC development [10].

### Silver diamine fluoride solution

Silver diamine fluoride (SDF) is an ammonia solution containing fluoride and silver ions. Laboratory studies have found that 38% SDF can slow dentine and enamel demineralisation and inhibit the growth of common cariogenic bacteria [11, 12]. Moreover, it preserves collagen from degradation in demineralised dentin [13]. Based on these mechanisms, SDF has been used worldwide to arrest ECC. Systematic reviews of clinical studies have found that 38% SDF solution (containing 44,800 ppm fluoride) is effective in arresting ECC [14, 15]. In addition, clinical trials found that SDF exerted a preventive effect on the entire dentition when it was applied to only decayed anterior primary teeth [16], and it was effective for preventing caries in permanent teeth [17]. Therefore, apart from its caries-arresting effect, some researchers have also advocated for SDF therapy as an important prevention-centred caries-management strategy during critical early childhood periods. Nevertheless, a literature search in PubMed and ClinicalTrials.gov databases revealed that no well-designed clinical trials have studied the preventive effect of SDF against ECC.

### Objective

The objective of this randomised clinical trial is to assess the effectiveness of 38% SDF solution and determine if it is superior to 5% NaF varnish in preventing new carious lesions in the primary anterior teeth of young children.

### Hypothesis

The hypothesis under investigation is that the biannual application (every 6 months) topical application of a 38% SDF solution on the primary upper anterior teeth is superior to that of a 5% NaF varnish in reducing the number of sound tooth surfaces that become cavitated caries in kindergarten children at 30-month follow-up.

## Methods/design

### Trial design

This is a phase II, single-centre, randomised, double-blind, active-controlled, parallel-group pragmatic trial. The design and report of this clinical trial protocol follows the Standard Protocol Items: Recommendations for Interventional Trials (SPIRIT) statement (Additional file 1) [18]. The trial schedule is shown in Fig. 1.

**Fig. 1 Fig1:**
[figure not shown]
The schedule of enrolment, interventions, and assessments. NaF sodium fluoride, SDF silver diamine fluoride

### Setting

The Faculty of Dentistry of the University of Hong Kong has been providing outreach dental services to local kindergartens. Invitations will be sent to these kindergartens to explain the purposes and procedures of this study. After receiving confirmation of participation from a kindergarten’s headmaster, informative consent forms will be distributed to the parents of the eligible children (Additional file 2). Written parental consent will be collected before the dental examination and treatment take place.

### Participants

All of the children attending their first year of kindergarten from the participating kindergartens will be invited to join this study. The inclusion criteria will be children who: 1) are aged 3 to 4 years old; 2) are generally healthy; and 3) have parental consent. The exclusion criteria will be children who: 1) are uncooperative with the dental examination and treatment; 2) have major systemic diseases, such as porphyria; or 3) are on long-term medication such as antiepileptic drugs.

### Baseline and follow-up oral examinations

All of the baseline and follow-up oral examinations will be conducted in the kindergartens, primarily through careful visual inspection with the aid of a World Health Organization (WHO) CPI probe (405/WHO probe, Otto Leibinger, Mühlheim, Germany) and a disposable front-surface dental mirror with light-emitting diode intraoral illumination (MirrorLite, Kudos Crown Limited, Hong Kong, China).

The six upper anterior teeth will be the studied teeth. They will be cleaned and dried with a gauze sponge before evaluation of their caries status. Caries will be diagnosed at the cavitation level. A surface without any cavitated lesions will be considered sound. The carious lesion will be gently explored with a CPI probe in the lesion’s centre. Great care will be taken to avoid tooth damage during the probing. A carious lesion will be recorded as active if softness is detected upon gentle probing. If the lesion is hard when probing, it will be classified as an arrested caries [16, 17]. The surface of each upper anterior tooth will be recorded as sound or carious (active or arrested). Apart from the studied teeth, the decayed, missing (due to caries) and filled primary tooth (dmft) index will be used to record each child’s caries experience (tooth level). Other tooth statuses, such as tooth discolouration and hypermobility, of all primary teeth will be recorded as well. Oral hygiene status will be measured using the visible plaque index [19]. The buccal and lingual surfaces of six index teeth (55, 51, 63, 71, 75 and 83) will be examined. The same examiner will conduct the follow-up oral examinations every 6 months for 30 months in the kindergartens using the same equipment, procedure and diagnostic criteria as those used in the baseline examination. The intraexaminer agreement on the caries and plaque assessment will be monitored and tested in 10% of the children at each stage of the study.

### Intervention

The children will receive either 38% SDF solution or 5% NaF varnish treatment on all of their upper anterior tooth surfaces. An independent operator will use a microbrush (MICROBRUSH, Grafton, WI, USA) to apply the SDF solution (Advantage Arrest, Elevate Oral Care, FL, USA) or NaF varnish (Duraphat Varnish, Colgate-Palmolive, NY, USA) according to the assigned treatment group. The SDF solution or NaF varnish will be applied once every 6 months for 30 months right after the oral examination. The kindergarten teacher will be instructed not to allow children in both groups to eat or drink for half an hour after the fluoride application. There will be no special criteria for discontinuing or modifying allocated interventions. Because the intervention is administered by a dentist, there are no strategies to improve adherence and monitoring of adherence. Implementing fluoride treatments will not require alteration to usual care pathways (including use of any medication) and these will continue for both trial arms.

### Randomisation, treatment allocation and allocation concealment

The participating kindergarten children will first be categorised as either: 1) having an increased caries risk, which is defined as having caries experience (dmft >0); or 2) having a low caries risk with no caries experience (dmft = 0). The children will then be allocated by a stratified randomisation method at the subject level with two strata (increased and low caries risk) using a personal computer into the following two groups in blocks of eight children for fluoride treatment every 6 months: group SDF (38% SDF solution) and group NaF (5% NaF varnish). There will be no negative control group for ethical reasons. A statistician will keep the random number sequence, and opaque sealed envelopes will be used to conceal the allocation sequence until the interventions are assigned.

### Blinding

In this randomised clinical trial, the examiner, the children and their parents will not be informed about the treatment group allocation throughout the study. Each assigned fluoride treatment will be applied after the oral examination by an independent operator. If parents request the treatment history of their child, unblinding is permissible. An unblinded research assistant will disclose treatment allocation to the parents, and the child will be excluded from the study.

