### Data management

Two people will independently enter the collected data into an Excel file (by double entry) and the data will be compared to minimise data entry errors. A statistician will oversee the data entry, data checking and analysis for this project. The intraexaminer agreement in caries diagnoses at each time point will be assessed using Cohen’s Kappa statistics. This trial will employ an intention-to-treat analysis. A per-protocol analysis will be performed if the number of children who stray from the protocol (for instance, by not adhering to the prescribed 6-month intervention, or by being withdrawn from active treatment) differs between the two groups. In that case, only the patients who complete the entire clinical trial according to the protocol will be counted towards the final results. Sensitivity analysis will also be considered by means of multiple imputations for missing values. The level of statistical significance for all two-sided tests will be set at 0.05. For one-sided tests, the level of statistical significance will be set at 0.025.

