## Data Availability

The data sets generated and/or analysed during the current study are available from the corresponding author on reasonable request. The results of each follow-up examination will be shared to each participant by a report to the parents. The interim and final results will be shared to other researchers by publications and presentations in international conferences.

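### Removing a randomised child when the parents ask for the treatment history contradicts the intention-to-treat analysis and loses the 30-month primary outcome, possibly in relation to that outcome

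*Protocol article*

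**What the plan says.** All references are to the protocol article.

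- **Blinding.** The examiner, the children and the parents are not told the allocation, and a separate operator applies the treatment after the examination. The exception is: "If parents request the treatment history of their child, unblinding is permissible". No clinical reason is required. The consequence is: "An unblinded research assistant will disclose treatment allocation to the parents, and the child will be excluded from the study".
- **Data management.** "This trial will employ an intention-to-treat analysis". No exception is made for unblinded children. A per-protocol analysis is conditional on deviations differing between the groups, and there "only the patients who complete the entire clinical trial according to the protocol will be counted towards the final results". On missing data: "Sensitivity analysis will also be considered by means of multiple imputations for missing values".
- **Outcome measure.** The primary outcome is whether surfaces of the six anterior teeth that were sound at baseline have developed caries at the 30-month examination.
- **Data Availability.** "The results of each follow-up examination will be shared to each participant by a report to the parents".

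**The concern.** Intention to treat keeps every randomised child in the arm assigned, whatever happens later. The Blinding rule removes some children because of a parental action that can occur at any time during the 30 months. Anyone carrying out the trial has to break one of the two statements.

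More than numbers may be lost. Parents are told what each examination found. A parent told of a new cavity has an obvious reason to ask what the child has been given. If that happens, children with new caries are over-represented among those removed, and the remaining children look healthier than the arm really is. If it happens at different rates in the two arms, the comparison is biased. The allowance of 20% for dropout replaces lost numbers. It does not correct selective loss.

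**Working it through.** **1. Can the passages be reconciled by reading?**

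| Reading of the Blinding rule | Consequence |
|---|---|
| The child's data are removed altogether | A randomised child is missing from the analysis: direct conflict with intention to treat |
| Earlier data are kept and only participation stops | No 30-month examination, so the primary outcome is missing; imputation is only to be considered, and only as a sensitivity analysis |

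Neither reading delivers the stated primary analysis. An analysis plan written later cannot recover examinations that were not done.

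**2. The plan's own sample size.** Inputs from Sample size calculation: means 0.47 (SD 0.87) and 0.70 (SD 0.84), two-sided 5%, power 0.90.

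- Pooled SD = √[(0.87² + 0.84²)/2] = 0.855; difference = 0.23.
- n = 2 × 0.855² × (1.960 + 1.282)² / 0.23² = 290.5, so 291 per group; the t-test version gives 291.5, so 292. The stated 292 is reproduced.
- 292/0.80 = 365 per group, 730 in total, as stated.

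Sample size is not the problem. A further 5% loss unrelated to outcome leaves 292 × 0.95 = 277 per arm and power 0.886.

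**3. Selective loss, no true effect (illustration).** From the documents: mean 0.70, SD 0.84, 292 per arm. Assumed: a share e = 5% of one arm is removed, all with new caries, and none in the other arm; the share of children with any new caries is a = 0.452 or 0.503. The upper value is what a Poisson count with mean 0.70 gives (1 − exp(−0.70) = 0.503); the lower is simply a second assumed value.

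- Mean among affected children = 0.70/a = 1.55 or 1.39.
- Remaining mean = (0.70 − e × 0.70/a)/(1 − e) = 0.655 or 0.664.
- Spurious difference = 0.045 or 0.036, that is 6.4% or 5.2% of 0.70.
- Second moment = 0.84² + 0.70² = 1.1956. Remaining variance = (1.1956 − e × 1.1956/a)/(1 − e) − (remaining mean)² = 0.690 or 0.693.
- SE = √[0.7056/292 + variance/(292 × 0.95)] = 0.070 in both cases.
- Chance of a false result favouring the depleted arm = P(Z > 1.96 − difference/SE) = 9.3% or 7.5%, against 2.5%.

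The same formulas give 3.9–4.4% at e = 2% and 19–27% at e = 10%. Note what e = 5% requires: 0.05/0.503 to 0.05/0.452, or 10–11% of affected families in one arm asking and none in the other.

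**4. The same loss in the NaF arm, planned effect.** The NaF mean falls from 0.70 to 0.655 or 0.664, so the difference falls from 0.23 to 0.185 or 0.194. SE = √[0.87²/292 + variance/277.4] = 0.071. Power = P(Z < difference/SE − 1.96) = 0.74 or 0.77, against the planned 0.90.

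**5. Equal requests.** If affected families ask at the same rate in both arms and there is no true effect, both means fall by the same amount and the expected difference is zero.

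**The case against.** The strongest reply is that the documents do not show outcome-related loss. They give no reason for requests and no rate, and the article does not connect the examination reports with unblinding. Data management also mentions children withdrawn from active treatment and restricts the analysis to completers only in the per-protocol case, which suggests that such children were meant to stay in the intention-to-treat set. The illustration loads every removal on one arm. All of this stands, and it limits what can be said about size and direction. It does not remove the conflict, because a child no longer examined has no 30-month outcome under any reading.

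Three stronger inferences are tempting and should not be drawn.

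- **That the bias favours SDF.** This would need SDF to cause visible changes that prompt more requests. The article records tooth discolouration among other tooth statuses but nowhere links it to SDF. If SDF works, more NaF children have new lesions, and requests could as well come mainly from that arm.
- **That the rule contradicts the Intervention section**, which says "There will be no special criteria for discontinuing or modifying allocated interventions". That sentence concerns changes to the allocated treatment, whereas the Blinding rule concerns membership of the study. The tension is weak.
- **That the eligibility criterion on children who "are uncooperative with the dental examination and treatment" also acts after randomisation.** The article does not say when cooperation is judged; it could be at the baseline examination before allocation.

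It is also fair to say that disclosure ends parental blinding, so keeping the child is not free of cost.

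**Conclusion.** The point holds as a contradiction between Blinding and Data management, with loss of the primary outcome for every child it touches. That part needs no modelling. That the loss may be related to outcome is a plausible inference from the reports to parents, not something the documents state.

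The size is unknown. Under the assumptions shown, 5% one-sided removal of affected children raises the false-positive chance in that arm's favour from 2.5% to about 7.5–9%; the same removal from the NaF arm under the planned effect cuts power to about 0.74–0.77; balanced requests with no true effect give no expected bias. These figures rest on the assumed request rate, the assumed 45–50% affected and complete one-sidedness. They show that a modest imbalance could matter, not that one will occur.

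**What to change.** Replace the exclusion rule in Blinding with wording such as:

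> Allocation is disclosed to the parents only. The date and reason are recorded. The examiner stays masked. The child remains in the 6-monthly examinations, unless the parents withdraw consent, and is analysed as randomised in the intention-to-treat analysis.

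Add to Data management a sensitivity analysis without the unblinded children, and report the number of requests by arm.

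This is workable because the examiner does not apply the treatment and a research assistant makes the disclosure. The proposal takes no position on whether allocated applications continue after disclosure.

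Cost: protocol wording and a short unblinding log. The examinations already take place in the kindergartens, and 292 evaluable and 365 recruited per group are unchanged. Downside: these parents are no longer blinded, which may alter their behaviour at home and their answers to the 30-month questionnaire. The sensitivity analysis shows how far the result depends on these children. It should stay secondary, since it brings back the same selection.

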### Outcome measure

The primary outcome measure will be sound surfaces of the six anterior teeth at baseline that develop or do not develop caries at the 30-month examination. The secondary outcomes measured will be the number of carious surfaces developed during the study that become arrested, caries experience (dmft index), increment in the number of nonvital teeth and number of hypermobile teeth at 30-month follow-up.

### Effect modification

A parental questionnaire that has been used in previous studies [3, 20] will be administered at baseline and again at the 30-month follow-up visit regarding their children’s oral hygiene habits (e.g. toothbrushing), fluoride agent use (e.g. fluoride toothpaste), diet habits (e.g. bottle feeding), snacking habits, dental visit behaviour, parental educational level, family income and family status (single- or both-parent households).

### Sample size calculation

The mean number of cavitated teeth of a 3-year-old child was five in our previous study [16]. The mean number of new cavitated caries surfaces found in the 62 children in the SDF group was 0.47 (standard deviation (SD) 0.87), and the mean new cavitated caries surfaces in the 61 children in the NaF group was 0.70 (SD 0.84) at the 30-month review. This difference corresponded to a prevented fraction of 33% more in the SDF group when compared to the NaF group, which is considered clinically significant. With the statistical power set at 0.9 and type I error rate of 5% for a two-sided test, the required sample size would be 292 for each group. Considering a dropout rate of 20%, the total number of children to be recruited at baseline should be 365 in each group. Therefore, a total of 730 children need to be recruited at baseline examination for this trial.

### Data management

Two people will independently enter the collected data into an Excel file (by double entry) and the data will be compared to minimise data entry errors. A statistician will oversee the data entry, data checking and analysis for this project. The intraexaminer agreement in caries diagnoses at each time point will be assessed using Cohen’s Kappa statistics. This trial will employ an intention-to-treat analysis. A per-protocol analysis will be performed if the number of children who stray from the protocol (for instance, by not adhering to the prescribed 6-month intervention, or by being withdrawn from active treatment) differs between the two groups. In that case, only the patients who complete the entire clinical trial according to the protocol will be counted towards the final results. Sensitivity analysis will also be considered by means of multiple imputations for missing values. The level of statistical significance for all two-sided tests will be set at 0.05. For one-sided tests, the level of statistical significance will be set at 0.025.

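### The per-protocol clause lets an undefined imbalance in deviations move the final result from intention-to-treat to completers only

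*Protocol article*

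**What the plan says.** The Data management section opens the matter without condition: "This trial will employ an intention-to-treat analysis". It then says: "A per-protocol analysis will be performed if the number of children who stray from the protocol" differs between the two groups. The examples of straying are missing the 6-monthly treatment and being withdrawn from active treatment. The consequence follows: "In that case, only the patients who complete the entire clinical trial according to the protocol will be counted towards the final results".

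The next sentence deals with missing data: "Sensitivity analysis will also be considered by means of multiple imputations for missing values".

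Two other places bear on the point. The abstract describes the design as a superiority trial: "This sample size will be sufficient for appropriate statistical analysis of a superiority trial with 90% power, allowing for a 20% drop-out rate". The Blinding section adds a post-randomisation exclusion when parents ask for their child's treatment history: "An unblinded research assistant will disclose treatment allocation to the parents, and the child will be excluded from the study".

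No sentence says that ITT stays primary once the condition is met, and none calls the PP analysis supportive.

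**The concern.** In a superiority trial the ITT comparison carries the claim because randomisation protects it. Here the set that counts towards the final results depends on something observed after randomisation, the arm-specific number of deviations.

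Three features make this a problem:

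- **The condition has no threshold.** Taken literally, any difference in counts triggers it. Otherwise someone decides what counts as a difference with the data in hand.
- **Straying may be related to outcome.** Missed applications and withdrawals can depend on the treatment received or on caries that has appeared. If that relation differs by arm, the completers are no longer comparable groups.
- **The wording is exclusive.** It says that only protocol completers count, and it refers to the final results rather than to an additional analysis.

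At stake is which set of children supports the claim that SDF is superior to NaF varnish. Selection could create a difference or hide one.

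**Working it through.** **1. The plan's own figures.** From the Sample size calculation section: means 0.47 (SD 0.87) and 0.70 (SD 0.84), two-sided 5%, power 0.9.

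- Difference: 0.70 − 0.47 = 0.23. Common SD: √[(0.87² + 0.84²)/2] = 0.855.
- The t-test calculation gives 291.5, so 292 per group. Then 292/0.80 = 365.

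Both stated figures reproduce. The point does not rest on a sample-size error.

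**2. How often a literal trigger fires.** Assume the same 10% straying rate in both arms, 365 children each, independent.

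- SD of the difference in counts: √(2 × 365 × 0.10 × 0.90) = 8.1.
- Chance of exactly equal counts: about 0.399/8.1 = 0.05.

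Read literally, the condition would be met about 95% of the time even with no real difference in adherence.

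**3. What the PP comparison can show with no true effect.** Assumptions, not in the documents:

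- both arms have mean 0.70 and SD 0.84, with 365 children per arm;
- a share q of children has at least one new lesion;
- 10% of children stray, except that a proportion p of SDF children with a new lesion stray;
- all strays are still examined at 30 months, so ITT would compare 0.70 with 0.70.

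Smallest q compatible with the NaF mean and SD. For whole-number counts of 1 or more, (X − 1)(X − 2) ≥ 0. With E[X²] = 0.84² + 0.70² = 1.1956, this gives q ≥ (3 × 0.70 − 1.1956)/2 = 0.452.

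Formulas for the SDF arm:

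- retained share k = 0.452(1 − p) + 0.548(0.90)
- PP mean = 0.70(1 − p)/k
- PP variance = 1.1956(1 − p)/k − (PP mean)²

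The NaF arm keeps 90% (328.5 children), mean 0.70, variance 0.7056.

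| | p = 0.30 | p = 0.20 |
|---|---|---|
| k, SDF | 0.810 | 0.855 |
| SDF children retained | 295.5 | 312.0 |
| PP mean, SDF | 0.605 | 0.655 |
| PP variance, SDF | 0.667 | 0.690 |
| Spurious difference | 0.095 | 0.045 |
| Spurious prevented fraction | 13.5% | 6.4% |
| Standard error | 0.0664 | 0.0660 |
| Difference / SE | 1.427 | 0.679 |
| Chance of false SDF win, Φ(ratio − 1.96) | 29.7% | 10.0% |

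The nominal chance is 2.5%. At p = 0.30, 19% of SDF and 10% of NaF children stray. The average is 14.5%, below the 20% dropout that the protocol plans for.

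**4. A second set of assumptions.** Let excluded children have r times the completers' mean, with an overall mean of 0.70 in both arms and SD 0.855. The completers' mean is 0.70/[(1 − f) + f·r] for excluded share f.

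| Excluded SDF / NaF | r | Spurious SDF benefit | Two-sided type I error |
|---|---|---|---|
| 20% / 20% | 1, 1.5 or 2 | 0 | 5.0% |
| 25% / 15% | 1.5 | 0.029 | 6.9% |
| 25% / 15% | 2 | 0.049 | 10.6% |
| 30% / 10% | 1 | 0 | 5.0% |
| 30% / 10% | 1.5 | 0.058 | 12.8% |
| 30% / 10% | 2 | 0.098 | 27.9% |

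The last row is 43% of the 0.23 design difference. If NaF loses more children, the sign reverses.

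**5. How much of this the switch causes.** If all strays drop out and have no 30-month outcome, an observed-case ITT loses the same children and shows the same 13.5%, so the switch adds nothing. If half of each kind of stray drops out, the observed-case ITT mean for SDF is 0.70 × 0.85/(0.452 × 0.85 + 0.548 × 0.95) = 0.658. That is a spurious 6.1%, against 13.5% under PP. Only with all strays examined does the whole 13.5% belong to the switch.

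**The case against.** **The sentence may only define the PP set.** The ITT statement is unconditional, the PP analysis is to be performed rather than performed instead, and the imputation sentence speaks of a further analysis. A reader who infers that the protocol has certainly abandoned ITT goes beyond the text. The objection still does not clear the wording. Counting only completers towards the final results fits poorly with a mere definition, and nothing says which analysis governs.

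**Unequal counts do not mean bias.** A reader might infer that the plan turns to PP exactly when PP is most biased. The documents do not support that. With exclusion unrelated to caries there is no bias whatever the imbalance, and equal counts can hide bias when the reasons differ by arm. This objection stands, and the point is limited accordingly.

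**The illustration is at the upper end.** The threefold straying rate among SDF children with new lesions is assumed, and part of the bias could be shared with an observed-case ITT. Both remarks stand.

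**Adherence data.** The Intervention section says "there are no strategies to improve adherence and monitoring of adherence", and a reader might infer that the trigger could never be evaluated. The stated reason is that a dentist gives the treatment, right after each examination. The natural meaning is that no separate adherence programme is needed, not that applications go unrecorded. No argument is built on it here.

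**The analysis plan may settle it.** The point concerns a rule that the article states, not a detail it leaves out. A plan that kept ITT final would have to depart from the natural reading of this sentence.

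**Conclusion.** The point holds in limited form. As written, the Data management section lets an undefined post-randomisation imbalance move the final result of a superiority trial from ITT to protocol completers. On the milder reading it leaves two candidate final results and a data-dependent choice between them. Either way the wording needs correction.

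The size depends on assumptions that the documents do not give. With no true effect and all strays examined at 30 months, the chance of a false SDF win is about 10% to 30% in the two cases worked, against 2.5% nominal, with a spurious prevented fraction of about 6% to 13.5%. Under other assumptions it is zero, or it favours NaF. The share caused by the switch shrinks as more strays are dropouts without a 30-month outcome. The sample size of 292 analysed and 365 recruited per group is unaffected.

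**What to change.** 1. Replace the completers-only sentence in Data management with:

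> The final result is the ITT comparison of all randomised children in their allocated group, whatever the number or balance of deviations; the per-protocol analysis is always reported as supportive and never replaces ITT.

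2. Delete the between-arm condition for performing the PP analysis.

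3. Make the multiple imputation already named there a committed analysis for missing 30-month outcomes. Without such a rule, an analysis of all randomised children cannot be carried out.

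4. Reconcile the Blinding section with the ITT statement, so that children unblinded at parental request stay in the ITT set wherever outcome data exist. This concerns the analysis set only.

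The cost is a few sentences in the protocol and the analysis plan, plus the work of the committed imputation. No extra children, visits or procedures are needed. The change should be made before arm-specific deviation counts are looked at alongside outcomes.
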